### Randomization

Participants (*N* = 1,180) will be allocated randomly into one of the two study groups at a ratio of 1:1. The allocation sequence will be generated by utilizing the ResMan Research Manager central randomization clinical trial management public platform (http://www.medresman.org/). The randomization will be stratified by study site. On the day of oocyte retrieval, investigators will log information into the web database using user identifications and passwords to obtain the randomization numbers and allocated groups for the eligible patients. Both investigators and participants will be aware of the allocations after oocyte retrieval.

### Outcome measurements

#### *Primary outcome*

The primary study endpoint is *live birth*, defined as delivery of any viable infant ≥28 weeks gestation after the first embryo transfer.

#### *Secondary outcomes*

Secondary efficacy parameters will include biochemical pregnancy, clinical pregnancy, implantation rate and ongoing pregnancy. *Biochemical pregnancy* will be defined as a serum β-hCG level ≥10 IU/L 2 weeks after embryo transfer. *Clinical pregnancy* will be defined as the presence of intrauterine gestation sac at 7 weeks gestation. *Ongoing pregnancy* will be defined as a viable pregnancy at 11 weeks gestation. Another secondary outcome will be cumulative live birth results (with each woman having only one allowable live birth) from the single IVF cycle. The safety endpoints will include OHSS, miscarriage, ectopic pregnancy, pregnancy complication, congenital anomalies and neonatal complications.

### Statistical analysis

#### *Sample size and power calculations*

Investigators in a recent study of Chinese infertile PCOS patients undergoing conventional IVF or ICSI with fresh embryo transfers reported that the live birth rate was 31.2 [21]. Imudia *et al.*, in their cohort study reported a live birth rate of 47.6 in cryothawed embryo transfer cycles [12]. In their randomized trial comparing fresh and frozen–thawed transfer in normal responders (average age = 33 years), Shapiro *et al.* (2011) demonstrated that the clinical pregnancy rate per transfer was 84.0 in the cryopreservation group and 54.7 in the fresh embryo transfer group. They reported that the ongoing pregnancy rates per transfer (at 10 weeks gestation) for these two groups were 78.0 and 50.9, respectively [22]. Shapiro *et al.* also showed that the clinical pregnancy rates per transfer in high responders were 79.6 in the cryopreservation group and 65.4 in the fresh embryo transfer group. They found that the ongoing pregnancy rates were 77.6% in the cryopreservation group and 65.4 in the fresh embryo transfer group [23]. In our present study, we plan to test the primary hypothesis of a difference of 10 in the live birth rate for the two randomization arms. Because all of the participants in this study are under 35 years old, we will assume that frozen–thawed embryo transfer will bring about a live birth rate of 40 and fresh embryo transfer will lead to a live birth rate of 30. A sample size of 530 prospectively enrolled participants in each randomization arm will yield a statistical power of 80 at a significance level of 0.01 to demonstrate an absolute difference in live birth rates of 10 between treatment arms. Taking into consideration a dropout rate of 10 (for example, due to canceled cycles or elective cryopreservation of embryos because of increased risk for OHSS), we will enroll 590 participants into each study group.

For the sample size calculations, the significance level will be set at α = 0.01 and the statistical power will be calculated as 1 - β = 0.80. The live birth rate in group A will be set at 0.30. The live birth rate in group B will set at 0.40. The ratio between groups will be 1:1. The minimum sample size will be 530 for each group, for a total of 1,060 participants. Taking into consideration a dropout rate of 10, we expect to ultimately have a total of 1,180 enrollees, with 590 participants in each group.

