### Interventions

Qualified patients will be randomized into either of two groups. Group A will undergo a fresh embryo transfer after ovarian stimulation, and group B will have all of their embryos cryopreserved after ovarian stimulation and then undergo a frozen–thawed embryo transfer. All of the participants will receive a standardized gonadotropin-releasing hormone (GnRH) antagonist ovarian stimulation protocol and luteal phase support.

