#### *Controlled ovarian hyperstimulation and oocyte retrieval*

The following list describes the COH and oocyte retrieval protocol:

1. *Baseline monitoring and initial dose determination*: Recombinant follicle-stimulating hormone (rFSH, Gonal-f; Merck Serono, Geneva, Switzerland) will begin on day 3 of spontaneous menses or cycle induced by exogenous progesterone or oral contraceptive pills. Baseline pelvic ultrasound and basal hormone levels—that is, serum FSH, luteinizing hormone, E2, progesterone and β-hCG test—will confirm an early follicular phase milieu. The initiation doses will be 112.5 IU/day for patients weighing ≤60 kg and 150 IU/day for patients weighing >60 kg.

2. *Ovarian response monitoring and rFSH dose adjustment*: At day 6 of ovarian stimulation, transvaginal ultrasound scans and serum hormone tests will be performed. rFSH doses will be adjusted according to ovarian response. Afterward, such monitoring will be performed either every other day or every day. Human menopausal gonadotropin (Menopur; Ferring Pharmaceuticals, St-Prex, Switzerland) may be added if necessary [18,19].

3. *GnRH antagonist starting time and dose*: GnRH antagonist (cetrorelix; Merck Serono, Darmstadt, Germany) at a daily dose of 250 μg by subcutaneous injection will begin when at least one follicle is ≥12 mm in mean diameter until the trigger day (including the trigger day).

4. *hCG trigger for final oocyte maturation*: hCG will be administered at a dose of approximately 4,000 to 8,000 IU by intramuscular injection when at least two follicles are ≥18 mm in mean diameter.

5. *Transvaginal ultrasound-guided oocyte retrieval*: Oocyte retrieval will be performed 36 hours after hCG injection.

On the oocyte retrieval day, qualified patients will be randomized. For patients assigned to group A, luteal phase support will be started just after follicular aspiration. For patients assigned to group B, no luteal phase support will be administered.

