#### *In vitro fertilization and embryo culture*

The oocytes will be inseminated approximately 4 to 6 hours after follicular aspiration. For the scoring of embryos at day 3, we will employ the Puissant *et al.* criteria, with a focus on the number and regularity of blastomeres as well as the percentage fragmentation [20]. Two embryos of top quality will be marked for the first transfer cycle. For patients assigned to group A, two embryos with top quality will be transferred on day 3, and the surplus embryos will been frozen on day 3 or day 5 according to the routine followed at different sites. For patients assigned to group B, all embryos will be cryopreserved and at least two embryos of top quality must be vitrified on day 3. To ensure that two viable, thawed day 3 embryos will be transferred in subsequent programmed cycles, obtaining one or two extra day 3 frozen embryos will be suggested in case frozen embryos lose their viability after thawing.

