#### *Type of analysis*

We will utilize an intent-to-treat approach to examine differences in the live birth rates for first embryo transfer cycle in the two treatment arms in the primary analysis by the Pearson *χ*^2^ test. Safety parameters and secondary efficacy parameters, such as pregnancy rate, OHSS rate and other rates, will be analyzed using the Pearson *χ*^2^ test and logistic regression (if necessary). Cox proportional hazards models and the Kaplan-Meier method will be applied to compare time to pregnancy and cumulative live birth rates.

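### Group A women frozen for OHSS risk are allowed for as dropouts, but intent-to-treat keeps them in group A, so the move from 530 to 590 per arm does not secure the stated 80% power

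*Protocol article*

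**What the plan says.** All places are in the protocol article.

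- **Sample size and power calculations.** Assumed live birth rates are 30% (fresh, group A) and 40% (frozen, group B), with α = 0.01. "A sample size of 530 prospectively enrolled participants in each randomization arm will yield a statistical power of 80"%. The number is then raised to 590 per arm for a "dropout rate of 10 (for example, due to canceled cycles or elective cryopreservation of embryos because of increased risk for OHSS").
- **Controlled ovarian hyperstimulation and oocyte retrieval.** "On the oocyte retrieval day, qualified patients will be randomized". The Randomization section gives 1,180 as the number randomised.
- **In vitro fertilization and embryo culture.** "For patients assigned to group A, two embryos with top quality will be transferred on day 3".
- **Interventions.** By design, "group B will have all of their embryos cryopreserved after ovarian stimulation".
- **Primary outcome.** Live birth is "defined as delivery of any viable infant ≥28 weeks gestation after the first embryo transfer". The definition does not require that transfer to be fresh.
- **Type of analysis.** The primary analysis is a Pearson chi-square test using an "intent-to-treat approach to examine differences in the live birth rates for first embryo transfer cycle".
- **Randomization.** "Both investigators and participants will be aware of the allocations after oocyte retrieval".

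**The concern.** Group A's transfer comes three days after randomisation. A decision in that interval to freeze everything because of OHSS risk changes the treatment of a woman already randomised. In group B the same decision changes nothing. The sample size section treats such a woman as lost and rests its 80% on 530 remaining women per arm, at an undiluted 30% versus 40%. The outcome definition and the intent-to-treat statement, read together, keep her in group A and count the birth from her frozen first transfer there.

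Dividing by 0.9 restores the number of women when some leave the analysis. It does nothing for a difference made smaller by women who remain. Two things are at stake. The planned power may not hold for the planned test. The word dropout also sits badly with intent-to-treat for one arm only, in a trial where allocation is known once oocytes have been retrieved.

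**Working it through.** **Inputs from the article.** Rates 0.30 and 0.40; α = 0.01, two-sided (Abstract); power 0.80; ratio 1:1; 530 and 590 per arm; allowance 10%; Pearson chi-square test.

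**Assumptions not in the article.** The share of group A converted to freezing, f; the live birth rate of converted women, set at the protocol's own frozen rate of 0.40 and varied in step 5; the split of the 10% allowance.

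**Formula.** With p̄ the mean of the two rates, power = Φ{ [ (pB − pA) − 2.576·√(2p̄(1−p̄)/n) ] / √[ (pA(1−pA) + pB(1−pB))/n ] }.

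**Step 1. Reproduce the plan.** For 0.30 versus 0.40 at n = 530: (0.10 − 0.07547)/0.02914 = 0.842, power 80.0%. The required n is 530. 530/0.9 = 589, stated as 590. The base calculation is correct. At n = 590 with no loss and no conversion: (0.10 − 0.07153)/0.02762 = 1.031, power 84.9%.

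**Step 2. Conversion only, nobody lost, n = 590.** Group A's rate is 0.30(1−f) + 0.40f = 0.30 + 0.10f; group B stays at 0.40.

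| Group A converted | Rate in A | Difference | Power |
|---|---|---|---|
| 0% | 0.3000 | 10.00 points | 84.9% |
| 2.5% | 0.3025 | 9.75 points | 82.6% |
| 5% | 0.3050 | 9.50 points | 80.1% |
| 10% | 0.3100 | 9.00 points | 74.5% |

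For the last row: (0.09 − 0.07176)/0.02774 = 0.658, power 74.5%. The threshold lies between 29 conversions of 590 (80.1%) and 30 of 590 (79.97%).

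**Step 3. Full 10% allowance, part conversion and part genuine loss.** Let the remaining 10% − f be removed from both arms. Then n = 590(0.90 + f) per arm, and group A's rate among those analysed is (0.27 + 0.40f)/(0.90 + f).

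- f = 0: n = 531, 0.300 versus 0.400, power 80.1%.
- f = 1%: n = 536.9, 0.3011 versus 0.400, power 79.5%.
- f = 3%: n = 548.7, 0.3032 versus 0.400, power 78.4%.

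**Step 4. Full 10% allowance, part conversion and part cancelled cycles.** Here cancelled cycles (share c in each arm) are kept and counted as no live birth. Group A's rate is 0.27 + 0.40f and group B's is 0.40(1−c). With f + c = 0.10 the difference is 0.10(1 − f − c) = 0.09 at every split.

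- All cancelled, 0.27 versus 0.36: power 77.5%.
- Half and half, 0.29 versus 0.38: power 75.9%.
- All converted, 0.31 versus 0.40: power 74.5%.

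**Step 5. Sensitivity to the converted women's live birth rate**, at 5% conversion with no other loss: 30% gives 84.9%, 35% gives 82.6%, 40% gives 80.1%, 45% gives 77.4% and 50% gives 74.5%.

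**The case against.** A reader might infer that using the 10% allowance puts power firmly at 74% to 78%. The article does not support that. The two causes are given only as examples, so withdrawal and loss to follow-up before delivery also fit the allowance. If all of the 10% were genuine losses, power would be about 80%, as stated. The 77.5% figure contains no frozen women at all; it rests on counting cancelled cycles as no live birth, a rule the article does not state. This objection stands, and it is why the result has to be a conditional range.

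Dilution also needs converted women to do better than the 30% fresh rate, and the article gives no rate for them. That stands as a condition. The 40% used here is the article's own figure for frozen transfer.

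Conversion of a full 10% may be an extreme. Women with severe OHSS during stimulation are excluded, starting rFSH doses are modest, and an antagonist protocol is used. These measures make heavy conversion less likely but do not rule it out, and the article itself names freezing for OHSS risk as a reason for the allowance.

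The 30% and 40% might be arm-level rates that already include some non-adherence. The hypothesis is worded for the randomised arms, but the next sentence ties each rate to the type of transfer. The text is ambiguous here, which weakens the point without removing it.

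Finally, recruitment is complete and intent-to-treat is already stated, so neither the sample nor the primary analysis need change. That is right, and it limits the remedy to the power statement and the label. Detailed endpoint rules, such as how to score a woman with no transfer, are commonly left to the full protocol or SAP and are not faulted here.

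**Conclusion.** The concern holds in a conditional form. The sample size section allows for post-randomisation freezing in group A as if those women left the analysis, while the outcome definition and the intent-to-treat statement keep them in. For that cause, the step from 530 to 590 does not protect the stated power.

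The shortfall is modest. With conversion alone, and a 40% live birth rate in converted women, the planned 80% survives up to 29 of 590 conversions and is lost from 30. With the full allowance used, power lies between about 80% (genuine losses only) and 74.5% (conversions only), a shortfall of 0 to 5.5 points. If converted women had only the 30% rate, conversion would cause no dilution.

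A reader might also infer that the trial is underpowered, or that converted women will be excluded from the primary comparison. The article supports neither. It gives no split of the 10%, and its analysis section commits to intent-to-treat.

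**What to change.** In the sample size section:

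1. Describe freezing for OHSS risk in group A as a departure from assigned treatment, not as dropout.
2. State that these women stay in group A in the primary intent-to-treat comparison.
3. Replace the flat 80% with power at 590 per arm under stated conditions: 82.6%, 80.1% and 74.5% at 2.5%, 5% and 10% conversion with no other loss; and, with the full allowance used, about 80% (all losses), 79.5% to 78.4% (1% to 3% conversions, the rest losses), 77.5% (all cancelled cycles counted as no live birth) and 74.5% (all conversions). Give the 40% assumption for converted women alongside, and say that at 30% there is no dilution.

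The change should be made before the outcome data are analysed; the Trial status section says follow-up is still under way. It costs a few sentences. No new data or visits are needed, randomisation is untouched, and the sample stays at 1,180. The downside is a slightly less favourable stated power.

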#### *Type of analysis*

We will utilize an intent-to-treat approach to examine differences in the live birth rates for first embryo transfer cycle in the two treatment arms in the primary analysis by the Pearson *χ*^2^ test. Safety parameters and secondary efficacy parameters, such as pregnancy rate, OHSS rate and other rates, will be analyzed using the Pearson *χ*^2^ test and logistic regression (if necessary). Cox proportional hazards models and the Kaplan-Meier method will be applied to compare time to pregnancy and cumulative live birth rates.

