**Methods/Design:**

This study is a multicenter, prospective, randomized controlled clinical trial (1:1 treatment ratio of fresh vs. elective frozen embryo transfers).. A total of 1,180 infertile PCOS patients undergoing the first cycle of *in vitro* fertilization (IVF) or intracytoplasmic sperm injection will be enrolled and randomized into two parallel groups. Participants in group A will undergo fresh embryo transfer on day 3 after oocyte retrieval, and participants in group B will undergo elective embryo cryopreservation after oocyte retrieval and frozen–thawed embryo transfer in programmed cycles. The primary outcome is the live birth rate. Our study is powered at 80 to detect an absolute difference of 10 at the significance level of 0.01 based on a two-sided test.

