## Methods/Design

In this multicenter, prospective, randomized controlled clinical trial (1:1 treatment ratio), live birth rates of fresh embryo transfer vs frozen–thawed embryo transfer are being compared in 1,180 infertile PCOS patients undergoing their first cycle of IVF or intracytoplasmic sperm injection (ICSI). Participants will be enrolled at 14 hospitals across mainland China. This study has been approved by the ethics committees at all study sites (listed in Additional file 1). Informed consent will be obtained from each patient before any study procedure is performed, in accordance with good clinical practice. Reporting of the study results will follow the 2010 revised CONSORT statement [13].

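### Randomisation is stratified by site at 14 hospitals, but the primary test of live birth is an unstratified Pearson chi-square: valid, slightly conservative, and easily improved

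*Protocol article*

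**What the plan says.** All references are to the protocol article.

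- **Methods/Design:** "Participants will be enrolled at 14 hospitals across mainland China".
- **Randomization:** "The randomization will be stratified by study site". Allocation is 1:1. Site is the only stratification factor named, and no block size is given.
- **Type of analysis:** the intention-to-treat primary analysis examines "differences in the live birth rates for first embryo transfer cycle in the two treatment arms in the primary analysis by the Pearson" chi-square test. Site is not mentioned. Logistic regression is named only for safety and secondary efficacy outcomes, to be used if needed, and without covariates.
- **Sample size and power calculations:** the calculation assumes live birth in 30% of women after fresh transfer (group A) and 40% after frozen transfer (group B), and aims for 80% power. On the error rate it says that "the significance level will be set at α = 0.01"; the abstract shows that this is two-sided. The result is 530 per arm, raised to 590 for 10% dropout.

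**The concern.** When allocation is balanced within each site, differences between sites cancel out of the comparison of arms. The true sampling variance of the difference in live birth rates is then the within-site variance only. A Pearson chi-square on the pooled two-by-two table uses the total variance, which includes the between-site part. If sites differ, its standard error is too large, its actual type I error falls below the nominal 0.01, and it has less power than a test that respects the strata.

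The point concerns a method that the article names, not a detail it leaves out. An analysis plan that followed the article would carry the mismatch forward, and one that used a site-stratified primary test would depart from the published protocol. At stake is a modest amount of precision in the primary result. The validity of a positive finding is not in question.

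**Working it through.** **Inputs from the article:** 30% v 40% live birth, two-sided α = 0.01, power 0.80, 1:1 allocation, 530 per arm, 14 sites, stratification by site.

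**Assumptions, not in the article:** the SD of live birth rates between sites, s, taken as 5, 10 or 15 percentage points around the mean of 35%; near-exact 1:1 balance within each site.

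**Step 1. Reproduce the plan's figure.** With the pooled two-proportion formula and no continuity correction:

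n = [z(0.995)·√(2·0.35·0.65) + z(0.80)·√(0.30·0.70 + 0.40·0.60)]² / 0.10²

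= [2.5758·√0.455 + 0.8416·√0.45]² / 0.01 = 529.95, so 530 per arm.

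This matches the stated 530, with power of 80.0% at that size. A one-sided test would give 456, a continuity correction 550, and an unpooled variance 526. So 530 is the size for the unstratified two-sided test the article names, with no credit taken for stratification. For dropout, 530/0.9 = 589, stated as 590.

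**Step 2. Variance.** Total variance per woman is 0.35·0.65 = 0.2275. Within-site variance is 0.2275 − s². The factor by which Pearson overstates the variance is R = 0.2275/(0.2275 − s²).

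- s = 0.05: 0.2275/0.2250 = 1.011
- s = 0.10: 0.2275/0.2175 = 1.046
- s = 0.15: 0.2275/0.2050 = 1.110

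**Step 3. Actual type I error of Pearson.** This is 2·[1 − Φ(2.5758·√R)].

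- s = 0.05: 2·[1 − Φ(2.590)] = 0.0096
- s = 0.10: 2·[1 − Φ(2.634)] = 0.0084
- s = 0.15: 2·[1 − Φ(2.714)] = 0.0067

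**Step 4. Power at 530 per arm, 30% v 40%.**

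Pearson: Φ{[0.10·√530 − 2.5758·√0.455] / √(0.45 − 2s²)}

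Stratified: Φ{[0.10·√530 − 2.5758·√(0.455 − 2s²)] / √(0.45 − 2s²)}

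| Site SD (points) | Pearson | Stratified | Forgone (points) |
|---|---|---|---|
| 0 | 80.0% | 80.0% | 0 |
| 5 | 80.1% | 80.5% | 0.4 |
| 10 | 80.5% | 82.1% | 1.6 |
| 15 | 81.3% | 84.8% | 3.5 |

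**Step 5. Check by simulation.** The set-up was 14 equal sites, 532 women per arm, exact balance within site and normally distributed site effects on the logit scale, with 100,000 runs under no effect and 40,000 under 30% v 40%. CMH is the Cochran-Mantel-Haenszel test by site.

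| Logit SD | 5th to 95th percentile of site rates | Type I error, Pearson | Type I error, CMH | Power, Pearson | Power, CMH |
|---|---|---|---|---|---|
| 0 | none | 0.0101 | 0.0100 | 80.2% | 80.2% |
| 0.2 | 28–43% | 0.0096 | 0.0100 | 80.0% | 80.3% |
| 0.3 | 24–47% | 0.0094 | 0.0102 | 80.7% | 81.3% |
| 0.5 | 19–54% | 0.0088 | 0.0107 | 81.1% | 82.8% |
| 0.7 | 14–61% | 0.0067 | 0.0098 | 81.5% | 84.5% |
| 1.0 | 8–71% | 0.0050 | 0.0094 | 82.3% | 87.6% |

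The simulation agrees with the formulas. With no site effect the stratified test costs essentially nothing. Pearson's power is at or above 80% in every row. Repeating the power runs with very unequal site sizes gave nearly the same gaps.

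**The case against.** The case for leaving the plan alone is substantial.

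- **The test is valid.** Its error is on the safe side, so it cannot raise the false-positive rate above 0.01. Stratification still balances the arms within sites whichever test is used, so it is not wasted. This stands.
- **Planned power is intact.** A reader might infer that the trial falls short of its stated power because of this test. The article does not support that: 530 was computed for this same test and reproduces exactly. What is forgone is a gain above the plan. Whether the dropout allowance fits the intention-to-treat analysis is a separate question and would not be caused by ignoring site.
- **The size is assumed and small.** The article gives no between-site spread. An SD of 15 points would put about 90% of site rates between 10% and 60% (35 ± 1.645·15), and nothing in the article suggests that. The conservatism also requires near-exact balance within site, and the article gives no block size. Both stand, and are carried as assumptions.
- **Evidence that sites differ is thin.** A reader might point to the section on embryo culture, which leaves freezing on day 3 or day 5 to site routine. That freedom covers only surplus embryos in group A. The primary outcome follows the first transfer, so this routine cannot affect it and does not support the point.
- **The article is condensed.** A site-adjusted analysis may be in a fuller document. That could add a supporting analysis, but the primary test named here would still be the unstratified one.

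These points limit the size of the concern. They do not remove it, because the stratified test matches the design, is no worse when sites do not differ, and is better when they do.

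**Conclusion.** The concern holds as a minor point of efficiency. The named primary test does not use the one factor on which randomisation is stratified. If site rates vary with an SD of 5 to 10 points around 35% and allocation is balanced within site, Pearson's variance is about 1% to 5% too large, its type I error is about 0.0096 to 0.0084, and 0.4 to 1.6 points of power are forgone. A loss of about 3.5 points needs a very wide spread. If sites do not differ, nothing is lost. There is no wrong figure, no internal contradiction, no inflated type I error and no shortfall from the stated 80% power.

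**What to change.** In Type of analysis, make the primary test a Cochran-Mantel-Haenszel test stratified by study site, and report the site-stratified risk difference with its confidence interval. Set a rule in advance for pooling very small sites, including the size threshold, so that no discretion is left to the analyst. Keep the Pearson chi-square as a sensitivity analysis. No further covariates are needed to settle this point.

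The sample size stays at 530 per arm (590 enrolled), and no extra data are needed. The cost is procedural: Trial status says that recruitment is complete and follow-up is continuing, and Randomization says that allocation is known to investigators and participants after oocyte retrieval. The change should therefore be a dated, documented amendment made before any outcome is compared by arm.

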### Participants

#### *Inclusion criteria*

The following are the inclusion criteria:

1. Women diagnosed with PCOS according to Chinese PCOS diagnostic criteria

2. Women who have a ≥1-year history of infertility

3. Women ages ≥20 and <35 years old

4. Women who have at least one of the following indications for IVF or ICSI:

a. Ovulation dysfunction and failure to become pregnant after ovulation induction treatment

a. Tubal factors: unilateral or bilateral tubal obstruction, adhesion, unilateral or bilateral salpingectomy or tubal ligation

a. Male factors: oligoasthenozoospermia or obstructive azoospermia

a. Women who are undergoing their first cycle of IVF or ICSI

a. Women whose retrieved oocytes number more than three

The Chinese PCOS diagnostic criteria are menstrual abnormality and either hyperandrogenism or PCO [14]. Menstrual disorders, including oligomenorrhea, amenorrhea or irregular uterine bleeding, are essential for the diagnosis of PCOS. *Oligomenorrhea* is defined as spontaneous cycle length ≥35 days. *Irregular uterine bleeding* is defined as spontaneous cycle length <21 days. *Amenorrhea* is defined as spontaneous cycle length ≥6 months. Hyperandrogenism is diagnosed on the basis of either hirsutism or hyperandrogenemia. Hirsutism is determined by a modified Ferriman–Gallwey score [15] >6 at the screening examination. *Hyperandrogenemia* will be defined as an elevated total testosterone level according to local laboratory criteria. Local cutoffs will be predetermined by each site prior to study initiation. *Polycystic ovarian syndrome* is defined as either an ovary that contains 12 or more follicles measuring 2 to 9 mm in diameter or increased ovarian volume (>10 cm^3^) [16]. Secondary causes of hyperandrogenism and ovulation dysfunction will be excluded before a PCOS diagnosis is confirmed, such as ovarian interstitial tumor or adrenal tumor, congenital adrenal hyperplasia, hyperprolactinemia and thyroid dysfunction.

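### The primary live-birth test is valid but unadjusted: it leaves out site and values recorded before randomisation, and so misses a small, nearly free gain in precision

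*Protocol article*

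**What the plan says.** The Type of analysis section fixes the confirmatory test: an intention-to-treat comparison of "the live birth rates for first embryo transfer cycle in the two treatment arms in the primary analysis by the Pearson" chi-square test. The next sentence mentions "logistic regression (if necessary", but only for safety and secondary efficacy parameters.

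Four items are known for every woman when she is allocated:

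- **Site.** The Randomization section makes it the only stratification factor. There are 14 hospitals.
- **Age.** It is an inclusion criterion, limited to 20 to under 35 years.
- **Weight.** It sets the starting dose: "112.5 IU/day for patients weighing ≤60 kg and 150 IU/day for patients weighing >60 kg".
- **Number of oocytes retrieved.** It is an inclusion criterion: "Women whose retrieved oocytes number more than three".

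The timing is explicit: "On the oocyte retrieval day, qualified patients will be randomized". The last three items are therefore true pre-randomisation values, although stimulation has already been given.

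**The concern.** In a randomised trial, adjusting for baseline values that predict the outcome removes part of the random variation in the treatment comparison. It needs no further patients. This plan holds three patient-level values and a stratification factor at allocation and uses none of them in its only confirmatory comparison. Nothing at patient level is balanced by design, so chance differences between arms in age, weight or oocyte yield stay in the estimate as noise.

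At stake is some precision on a 10-point target tested at a strict significance level. The question is how much.

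**Working it through.** **Inputs from the protocol.** Live birth 30% in the fresh arm ("The live birth rate in group A will be set at 0.30") and 40% in the frozen arm; 1:1 allocation; testing "at the significance level of 0.01 based on a two-sided test" (Abstract); "the statistical power will be calculated as 1 - β = 0.80" (Sample size and power calculations); 530 per group, or 590 with 10% dropout.

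**Input not in the protocol.** The share R² of live-birth variance explained by the adjustment variables. It is assumed here to be 0% to 5%.

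**Step 1: reproduce the planned size.** With pooled variance and no continuity correction,

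n = [z(0.995)·√(2 × 0.35 × 0.65) + z(0.80)·√(0.30 × 0.70 + 0.40 × 0.60)]² / 0.10²

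= [2.576 × 0.6745 + 0.8416 × 0.6708]² / 0.01 = (1.7375 + 0.5646)² / 0.01 = 530 per group.

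This matches the stated figure exactly. Dividing by 0.9 gives 589, against the stated 590. The size was therefore calculated for the unadjusted test that is planned.

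**Step 2: effect of adjustment.** Approximate it as an effective size n/(1 − R²), with power = Φ[(0.10·√n_eff − 1.7375) / 0.6708].

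| Assumed R² | Power, 530 per arm | n per arm for 80% power | Power, 590 per arm |
|---|---|---|---|
| 0% | 80.0% | 530 | 84.9% |
| 1% | 80.5% | 525 | 85.3% |
| 2% | 81.0% | 520 | 85.7% |
| 3% | 81.4% | 515 | 86.1% |
| 5% | 82.4% | 504 | 87.0% |

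Example for 5%: n_eff = 530/0.95 = 557.9, and Φ[(2.3620 − 1.7375)/0.6708] = Φ(0.931) = 82.4%.

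**Step 3: check by simulation.** 530 per arm, 6,000 runs per case, one standard-normal covariate, chi-square (as a pooled z-test) against the adjusted logistic Wald test:

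- Odds ratio 1.0 per SD (R² 0): 80.0% against 79.9%. A useless covariate costs nothing noticeable.
- Odds ratio 1.25 per SD (R² about 1%): 80.0% against 80.5%.
- Odds ratio 1.5 per SD (R² about 3%): 79.7% against 80.9%. The SD of the risk difference falls from 0.0289 to 0.0285.

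The mean risk difference was 0.10 with and without adjustment. Under no effect, with a covariate of odds ratio 1.5 per SD, the unadjusted test rejected in 1.02% of runs against the nominal 1%.

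**Step 4: size of a chance imbalance.** For a covariate score with log-odds effect β per SD, an imbalance of 2 standard errors at 590 per arm shifts the unadjusted difference by about 2 × √(2/590) × β × 0.35 × 0.65. For assumed β of 0.25 to 0.45 (R² about 1.4% to 4.3%) this is 0.7 to 1.2 percentage points. The standard error of the difference is √(0.45/590) = 2.8 points, so the shift is 0.24 to 0.43 of a standard error.

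Site was not simulated. In the table it counts as part of the total R². Where stratification has already balanced a prognostic site effect, the unadjusted test tends to be slightly conservative; it is not invalid.

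**The case against.** The case for leaving the plan alone is substantial.

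- **The test is sound.** A reader might infer that an unadjusted primary test is wrong, or that the trial is underpowered because of it. The protocol does not support either reading: the test holds its level, its estimate is unbiased, and the sample size was derived for it. This stands in full.
- **Imbalance is not bias.** A reader might also infer that an uneven split of age or oocyte yield would distort the result. It adds random variation that the unadjusted standard error already covers. Adjustment removes part of that variation and corrects no bias. This stands too.
- **Prognostic strength is not shown.** The sample-size section reasons from age under 35, which implies that age matters, but gives no association. The age range is narrow, and both arms are planned to receive two embryos at first transfer, so oocyte number may say little. The fresh-transfer ongoing pregnancy rates cited for normal and high responders (50.9 and 65.4) come from different trials, and the matching frozen-transfer rates barely differ (78.0 and 77.6). The range of gain must therefore start at zero.
- **Timing.** Recruitment ended in April 2014 and allocation is known to investigators and participants. Changing a published primary test now can look influenced by data. This is a real cost.
- **Only an article is at hand.** The full protocol or analysis plan may hold a supportive adjusted analysis. That would not alter the point, because the article itself names the confirmatory test.

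What remains is that the variables are already recorded, adjustment cannot introduce post-randomisation bias, and the simulation shows no noticeable loss if they prove uninformative.

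**Conclusion.** The point holds as a low-priority improvement. The primary comparison uses neither the stratification factor nor the patient-level values on record before allocation.

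Under the assumption that these explain 0% to 5% of live-birth variance, the gain is 0 to 2.4 points of power at 530 per arm (80.0% to at most about 82.4%), equal to at most 530 − 504 = 26 women per arm. If all 590 per arm are analysed, power goes from 84.9% to at most about 87.0%. The upper limits depend wholly on the assumed R², for which the protocol gives no figure. The 590-per-arm figures also assume that every randomised woman contributes an outcome at the planned rates.

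The 80% figure belongs to 530 analysed per arm, after the dropout allowance. An analysis of everyone randomised does not sit on so tight a margin.

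**What to change.** In Type of analysis, before database lock and without sight of outcomes by arm, define the primary estimate in all randomised women as follows:

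- logistic regression of live birth on arm, site, age, weight and number of oocytes retrieved, with the last three continuous;
- reported as a standardised (marginal) risk difference, which keeps the 10-point absolute target, with a 99% confidence interval;
- tested at two-sided 0.01.

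Keep the Pearson chi-square as a reported sensitivity analysis.

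The cost is one sentence and one extra model, with no new data or patients. The Trial status section says that follow-up is ongoing, so there may still be time. The small downside is that the change follows recruitment in an open-label trial. It must be dated and documented as made without outcome data by arm.
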